### 2.9. Measures

#### 2.9.1. Process Measures

We operationalised measures of study processes as follows:Participant recruitment and retention:○Proportion of students in participating classes completing the baseline survey;○Proportion of students in participating classes completing the follow-up survey;○Proportion of students in participating classes completing both baseline and follow-up surveys.Data collection:○Proportions of students participating in the online and paper–pencil surveys;○Problems during data collection.Data quality:○Proportion of missing data for outcome and sociodemographic measures;○Basic psychometric properties of scales used to assess programme effectiveness (Table 1) including scale distributions, floor and ceiling effects and internal consistency.

#### 2.9.2. Outcome Measures

Our selection of the primary and second outcomes was guided by the SIMPEA model (Table 1) [36]. Given that validated scales for assessing most outcomes were not available in German, we relied on items translated and adapted from international studies. When suitable items were not available, new items were created by the study team. The student survey is provided in a supplementary online appendix.

#### 2.9.3. Sociodemographic Measures

Sociodemographic data were assessed at baseline and included age, gender, parental educational attainment, municipal size and subjective social status using the German version of the MacArthur Scale [57].

### 2.10. Data Collection

Data were collected in both intervention and control classes one week before and one week after the PCS (Figure 1). Students accessed and completed an online survey (Unipark Version 21.2, QuestBack GmbH, Oslo, Norway) at both time points via a link/QR code provided in the invitation leaflet, using their private devices during school hours. A paper-and-pencil version with the same content was also offered. To minimise loss to follow-up, we sent two reminders to encourage participation. Teachers were invited to complete a teacher protocol sheet assessing the number of eligible students and problems during the evaluation process.

### 2.11. Sample Size Considerations

Recent methodological evidence suggests that feasibly sized pilot studies for cluster randomised trials typically lack precision in reliably estimating recruitment and retention rates and estimates of sample sizes are biased downwards [58]. Sample size considerations for the pilot study were thus geared towards requirements for investigating data collection and data quality for which no formal statistical guidance exists. We therefore pragmatically aimed to recruit 15 school classes with 10–15 students each, yielding a total sample of 150–225 consenting participants.

### 2.12. Analysis

To assess participant retention, we will examine differences between the retained subsample (data provided on both assessments) and the subsample lost to follow-up regarding baseline values of sociodemographic and outcome measures using a dichotomous retention variable and logistic regression models. Proportions of students participating in the online and paper–pencil survey modes will be analysed descriptively. Problems during data collection will be abstracted from reports submitted by teachers and structured thematically to improve the implementation of the future effectiveness and process evaluation.

To uncover missingness patterns [59], missing data will be assessed across different variables. To detect potential missingness mechanisms, we will investigate associations between dichotomous variables identifying respondents with missing data and sociodemographic measures using logistic regression models. Cronbach’s alpha will be used to investigate internal consistency of scales. After computing mean scores, scale distributions as well as floor and ceiling effects will be analysed descriptively.

In a randomisation check, we will examine the balance of outcomes and sociodemographic measures in the baseline data between the intervention and control arm. The continuous primary outcome (intentions of students to reduce their ecological footprint) will be compared between the intervention and control arm with an intention-to-treat analysis using a linear mixed model containing a dichotomous intervention group variable and a random effect for school classes to account for the nested data structure [60]. Secondary outcomes will be compared between the two study arms using analogous linear mixed models.

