Third, the pilot study takes place amidst the COVID-19 pandemic, potentially affecting response rates due to, inter alia, non-attendance of students following mandatory quarantine measures or COVID-19 infections, thus limiting the generalisability of our findings. However, we anticipate that more students will attend schools during non-pandemic times, therefore rendering response rate estimations from the pilot study conservative. Forth, we acknowledge that no formal programme theory has been developed a priori to guide expectations how the PCS may be related to outcomes or interact with contextual factors. For programmes primarily developed by practitioners, however, recent guidance on the evaluation of complex interventions suggests that programme theory in these cases is often developed in parallel with the evaluation cycle [28]. We therefore plan to explore the applicability of the SIMPEA as programme theory for the PCS in a formative qualitative study comprising semi-structured interviews with students, teachers, school principals and members of the implementation team followed by transdisciplinary workshops. If suggested by interview and workshop results, we will develop the programme theory further by, inter alia, proposing outcomes not currently considered in the SIMPEA [36], mechanisms linking the PCS to outcomes and contextual factors at the level of students, teachers and schools that hinder or promote PCS implementation and potentially moderate intervention effectiveness. However, given the strong alignment of the SIMPEA with the objectives of the PCS, we anticipate that relatively minor adaptations to the original model will be necessary. Last, we acknowledge that different approaches may have been used at several points in designing this study. Given that the current understanding of issues explored in this study is limited and that our goal was to lay the groundwork for future work, we focused on foundational, yet methodologically important operationalisations of study processes, such as the proportion of students completing both baseline and follow-up surveys, providing a measure of participant retention, and the proportion of missing data and basic psychometric properties of scales, highlighting potential problems with data quality as well as floor and ceiling effects, respectively. We consider this pilot study as a learning opportunity for gauging the feasibility and potential implications of several methodological decisions made at this stage, potentially guiding the design and implementation of related research projects in Germany and internationally.

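### The retention and missing-data logistic regressions name neither school class nor study arm: intervals for age and municipal size may be too narrow, and no described analysis compares retention by arm

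*Protocol article*

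**What the plan says.** Recruitment and retention, data collection and data quality are the primary objectives (Objectives; section 3, Discussion). Section 2.12 sets out two sets of logistic regressions for them.

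- **Retention:** retained and lost students are compared "regarding baseline values of sociodemographic and outcome measures", "using a dichotomous retention variable and logistic regression models".
- **Missing data:** "we will investigate associations between dichotomous variables identifying respondents with missing data and sociodemographic measures using logistic regression models".

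Neither description mentions class, a cluster-robust variance or study arm. In the same section the primary outcome model includes "a random effect for school classes to account for the nested data structure", and the secondary outcomes follow by analogy. The abstract shows the same contrast: logistic regression for missingness, mixed models for outcomes.

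Arm appears in section 2.12 in two places only: the outcome comparisons, and the baseline check, where "we will examine the balance of outcomes and sociodemographic measures in the baseline data between the intervention and control arm". The retention proportions in section 2.9.1 are defined over all participating classes, not by arm.

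**The concern.** The plan allows for nesting in its secondary objective but does not say that it does so in models serving its primary ones.

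**Class.** Students completed the online survey "using their private devices during school hours", and the Limitations anticipate "non-attendance of students following mandatory quarantine measures or COVID-19 infections". Such absences can remove several classmates at once, so clustering of loss by class is plausible. For items left blank by students who did respond the case is weaker, because quarantine does not explain them. The classes span grades 7 to 13, so age largely follows class. Municipal size varies mainly between the five schools. Ignoring clustering matters most for predictors of this kind.

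**Arm.** Students and teachers know the allocation (section 2.8), controls wait three weeks for the programme (2.1), and teachers with a single class chose its arm freely (2.7). Loss could differ between arms, which bears on the intention-to-treat comparison and on the main trial's design. A model without arm cannot show it.

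At stake is guidance for the main trial: apparent predictors of dropout that are only class effects, and no analysis of arm-related loss.

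**Working it through.** **Inputs from the article.** 12 classes in five schools, seven intervention and five control (2.1). Planned size: 15 classes of 10–15 students (2.11). Check: 15 × 10 = 150 and 15 × 15 = 225, as stated. With the 12 classes obtained, the same class sizes give 12 × 10 = 120 to 12 × 15 = 180.

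**Assumed, because the article gives no figure.** The intraclass correlation (ICC) of dropout, the retention rate, and a two-sided 5% test.

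**Step 1: formula.** For class size m, the design effect is DE = 1 + (m − 1) × ICC(dropout) × ICC(predictor). The true error of a nominal 5% test is 2 × [1 − Φ(1.96/√DE)]. For a predictor constant within class, ICC(predictor) = 1:

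| Dropout ICC | DE, m = 10 | DE, m = 15 | True type I error |
|---|---|---|---|
| 0.05 | 1 + 9 × 0.05 = 1.45 | 1 + 14 × 0.05 = 1.70 | 10–13% |
| 0.10 | 1.90 | 2.40 | 16–21% |
| 0.20 | 2.80 | 3.80 | 24–32% |

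For a predictor that varies only within class, ICC(predictor) = 0, DE = 1 and the error stays at 5%.

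**Step 2: simulation of ordinary logistic regression.** 12 classes of 12, a normal class effect on the logit scale, a null predictor, 2,000 runs per cell. Rejection rates at latent ICC 0.05 / 0.10 / 0.20:

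| Null predictor | 75% retained | 90% retained |
|---|---|---|
| Varies within class only | 5.3 / 4.2 / 4.8% | 5.1 / 5.4 / 4.4% |
| Predictor ICC 0.1 | 5.6 / 4.8 / 5.8% | 4.8 / 4.6 / 5.0% |
| Predictor ICC 0.5 | 7.0 / 8.7 / 12.6% | 6.2 / 6.4 / 8.0% |
| Constant within class | 8.4 / 12.8 / 19.8% | 6.0 / 9.6 / 11.0% |
| Arm (7 v 5 classes) | 8.8 / 13.7 / 20.3% | 5.8 / 7.5 / 11.5% |

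The simulated rates are below the formula's. The simulation sets the ICC on the latent logit scale, and the same latent value means weaker correlation in the observed yes/no outcome. The conclusion uses the lower, simulated figures. The last row shows that adding arm without allowing for class would itself produce false positives.

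**Step 3: does the remedy work?** Generalised estimating equations (GEE) clustered on class, with bias-reduced variance and a t reference on 10 degrees of freedom, were run 600 times per cell with about 25% lost. At ICC 0.05 / 0.10 / 0.20 they rejected a null age-like predictor in 5 / 4 / 3% of runs and null arm in 4 / 4 / 4%. Ordinary logistic regression in the same runs gave 10 / 10 / 19% and 10 / 14 / 20%.

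For a predictor that varies by school the remedy is weaker. With assumed class and school ICCs of 0.05–0.10, a hypothetical split of classes over schools and 400 runs, the class-clustered GEE rejected in 9–13% of runs with a normal reference and 5–8% with t on 10 degrees of freedom.

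**The case against.** The best defence is that this is a condensed article. It names logistic regression without giving a covariance structure, and a fuller plan could add clustering. A reader might infer that the article states that students are independent. It does not; that is inferred from the contrast with the mixed model a paragraph later. The contrast is strong enough to ask for a change, but not to call it a stated error.

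Other stronger readings also fail:

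- **Differential attrition is never examined.** This cannot be confirmed. The flowchart (Figure 1) is not shown in the text available and may give follow-up by arm. What can be said is that no analysis described in the text compares retention or missingness by arm.
- **The models contradict the plan for survey mode.** They do not. The Discussion ties the choice of mode to uptake, weighed against burden on schools, and section 2.12 analyses mode proportions descriptively.
- **Teachers supervised the surveys, so clustering is certain.** Section 2.10 does not say so.
- **All predictors are affected.** Gender hardly is. Parental education, social status and baseline outcomes are less exposed than age and municipal size.

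The consequences are also limited. The models carry no alpha or decision rule, section 2.11 concedes that such pilots estimate retention imprecisely, and the Discussion will combine pilot rates with external evidence. An arm coefficient from seven against five classes, partly allocated by teacher choice, is weak evidence about the main trial. These points lower the severity. They do not justify leaving class and arm out of analyses that serve primary objectives.

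**Conclusion.** The point stands, at moderate severity. As described, the retention and missingness models omit class and arm. If loss clusters by class, a nominal 5% test of a class-level predictor has a true error of about 8–20% at 75% retention and 6–11% at 90%, over assumed latent ICCs of 0.05–0.20. Within-class predictors stay near 5%. The size rests on ICCs and retention rates that the article does not give, and on clustering that is plausible for retention but less clear for item missingness. The absence of an arm comparison from the described analyses does not depend on those assumptions. The harm would be misleading guidance for the main trial, not a wrong conclusion on effectiveness.

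**What to change.** In section 2.12, for both sets of models:

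1. Allow for class, by a random intercept or by GEE clustered on class with a small-sample variance correction and a t reference.
2. Add study arm as a predictor, together with the class adjustment and not in place of it.
3. Tabulate retention and missingness by arm and by class. The teacher protocol sheets (2.10) ask for the number of eligible students and can supply class denominators where returned.
4. State that the results are descriptive, given 12 classes in five schools, and read school-level predictors such as municipal size with particular caution, because clustering on class alone may not fully correct them.

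Survey mode may be added as a predictor, but the plan's stated use of mode does not require it.

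The cost is analysis wording and code, with no new data. The downside is wider intervals for age, municipal size and arm.

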## Abstract

**Introduction:** School-based programmes may promote knowledge and skills required to address climate change and better health and well-being in adolescents, yet evidence of their effectiveness is limited. In preparation for evaluating the Public Climate School, a school-based intervention to promote climate awareness and action in adolescents, we conduct a pilot study intended to assess procedures for participant recruitment, retention, and data collection, data quality issues and to provide preliminary parameter estimates to guide sample size calculations. **Methods and analysis:** This unblinded, cluster-controlled pilot study targets students in twelve classes from grades seven to thirteen in German public schools. Seven and five classes were allocated to the intervention and waitlist control arms, respectively. The intervention consisted of (1) live lessons on YouTube, (2) climate-related challenges of the day, (3) workshops and (4) peer exchange sessions. Waitlist control classes participated three weeks later. Measures included the proportion of students completing baseline and follow-up surveys, a comparison of baseline characteristics between students in the retained subsample and those lost to follow-up, proportions of students completing online and paper–pencil-based surveys and problems during data collection based on information reported by teachers. Data quality was assessed as proportions of missing data, associations between missingness and sociodemographic measures using logistic regression models and basic psychometric properties of scales including ceiling effects and internal consistency. Intentions to reduce one’s ecological footprint, the primary outcome, and all secondary outcomes for effect estimation were assessed one week pre- and post-intervention from November to December 2021 using items adapted from internationally used instruments and will be investigated using generalised linear mixed models and intention-to-treat analyses. **Conclusions:** The pilot study will lay the methodological groundwork for a large-scale cluster-randomised effectiveness and process evaluation of the Public Climate School. If proven effective and rolled out more broadly, the Public Climate School has the potential to contribute meaningfully to national climate mitigation and adaptation efforts by reaching a substantial share of adolescents in public schools, including those traditionally less involved in climate action.

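### The item-missingness models use only sociodemographic predictors, so they can show only indirectly whether skipped items depend on students' observed climate intentions or attitudes

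*Protocol article*

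**What the plan says.** Section 2.12 of the protocol article describes two sets of logistic models.

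- **Retention.** Students with data at both surveys are compared with those lost to follow-up "regarding baseline values of sociodemographic and outcome measures using a dichotomous retention variable and logistic regression models".
- **Missing data among respondents.** The purpose is given as "To detect potential missingness mechanisms", and the method is: "we will investigate associations between dichotomous variables identifying respondents with missing data and sociodemographic measures using logistic regression models". The Abstract repeats the restriction: "associations between missingness and sociodemographic measures using logistic regression models".

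Section 2.9.3 lists the predictors available to the second set: "Sociodemographic data were assessed at baseline and included age, gender, parental educational attainment, municipal size and subjective social status". Descriptively, section 2.12 adds that "missing data will be assessed across different variables", and section 2.9.1 lists as a data-quality measure: "Proportion of missing data for outcome and sociodemographic measures". According to the Abstract, the primary and all secondary outcomes were measured before as well as after the intervention, so baseline outcome scores exist. Data quality is one of the three primary objectives.

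**The concern.** A model that asks whether missingness depends on observed data can detect only dependence on the variables entered in it. For missing outcome items, the observed variables closest to the missing values are the baseline outcome scores and, within one survey, the scales the student did answer. The plan treats baseline outcomes as relevant to who is lost between surveys. It leaves them out when asking which respondents have missing items, and gives no reason.

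The restriction is stated twice, in the Abstract and in section 2.12. It is a choice that the article makes, not a detail left to a fuller document.

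What is at stake is how a null or weak result is read. If skipping is related to climate intentions or attitudes but hardly to sociodemographic background, the planned models would show little. A reader could then conclude that item missingness is unrelated to the constructs being measured, when the analysis had no direct means of showing otherwise.

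**Working it through.** **Side by side (section 2.12)**

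| | Retention models | Missing-data models |
|---|---|---|
| Dependent variable | Retained or lost to follow-up | Respondent has missing data or not |
| Sociodemographic predictors | Yes | Yes |
| Baseline outcome predictors | Yes | No |
| Stated aim | Differences between retained and lost students | Possible missingness mechanisms |

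The set with the more ambitious aim has the narrower set of predictors.

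**Sample size.** The plan's only figure, in section 2.11, reproduces: 15 × 10 = 150 and 15 × 15 = 225. The twelve classes recruited (section 2.4) at the same class size would give 12 × 10 = 120 to 12 × 15 = 180. The article gives no expected missing rate, effect size or power for these models, so what follows is illustration only.

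**Closed-form illustration.** Assumed: n = 150; 15% of respondents with missing items; odds ratio 2 per SD of lower baseline intention; correlation 0.2 between intention and one sociodemographic score; two-sided alpha 0.05; students independent.

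- SE of the log odds ratio per SD = 1/√(150 × 0.15 × 0.85) = 1/√19.125 = 0.229.
- Baseline intention as predictor: z = 0.693/0.229 = 3.03; power ≈ Φ(3.03 − 1.96) = 0.86.
- Sociodemographic proxy: log odds ratio ≈ 0.2 × 0.693 = 0.139, odds ratio 1.15; z = 0.139/0.229 = 0.61; power ≈ 0.09.
- Range over the correlation: at 0, power is 0.05 (alpha itself); at 0.4, log odds ratio 0.277, z = 1.21, power ≈ 0.23.

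**Simulation check.** 1,000 runs per setting, n from 120 to 225, odds ratio 0.5 per SD of higher engagement, about 19% skipping, class clustering ignored.

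| Predictor | Correlation with engagement | Estimated odds ratio | Share of runs detecting the dependence |
|---|---|---|---|
| Sociodemographic score | 0 | 1.00–1.01 | 4–5% |
| Sociodemographic score | 0.2 | 0.87–0.88 | 9–11% |
| Sociodemographic score | 0.4 | 0.76–0.77 | 18–32% |
| Baseline engagement | – | 0.48–0.50 | 77–97% |

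The two calculations agree. If the dependence exists, a proxy usually misses it, even at a correlation of 0.4. Neither calculation says that the dependence does exist.

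**Room for extra predictors.** At 15% missing, 150 students give 150 × 0.15 = 22.5 events; 120 to 180 students give 18 to 27. Five sociodemographic measures plus intention, concern and denial, at one parameter each, make 8 parameters, or 22.5/8 ≈ 2.8 events per parameter. One large joint model is therefore not a sensible remedy.

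**The case against.** The strongest reply is that much is already covered. Loss of whole surveys is modelled on baseline outcome measures, and missing data are described across variables. The aim speaks only of potential mechanisms, and the analysis is exploratory. The Discussion says the missing-data assessment is meant to improve the structure and content of the survey. This stands, and it confines the point to item missingness among respondents. It does not explain why predictors used in one set of models are left out of the other.

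Three stronger readings are tempting, and the documents do not support them.

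- A reader might infer that students who skip sociodemographic questions are dropped from these models. Section 2.12 states neither a complete-case rule nor that the five measures enter jointly, and such handling may be set out in a fuller document. Section 2.9.1 lists missing sociodemographic data as something to measure; it does not predict it.
- A reader might infer that low climate engagement is the main reason for skipping. Nothing in the article says so. Survey mode, device, questionnaire length or reading ability could matter as much. The point needs only that dependence on engagement is possible and not directly examined.
- A reader might infer that the main trial would inherit wrong missing-data assumptions. The Discussion bases sample size planning on parameter estimates, ICCs, and recruitment and retention rates, combined with external evidence. It does not say that these models set missing-data assumptions.

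It is also fair to object that the power figures rest on invented inputs, and that the direct-predictor figure applies to one fully observed predictor. At baseline, the intention score may itself be missing.

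**Conclusion.** The point holds in limited form. The item-missingness models are restricted to sociodemographic predictors, which does not match their stated aim or the retention models in the same section. They can register dependence on observed climate intentions or attitudes only through correlation with sociodemographic measures, so a null result would leave that question open.

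The size cannot be taken from the article. On the assumptions shown, detection through a proxy is roughly 4% to 32%, against 77% to 97% with the baseline score itself. These figures depend on the assumed odds ratio, missing rate and correlation, and they ignore clustering by class, so they show the direction of the problem and not its amount.

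The matter is modest: an exploratory analysis, but one that serves a primary objective and can be corrected with data already collected.

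**What to change.** - **Item missingness at follow-up:** add the baseline primary outcome score, and the baseline concern and denial scores, as predictors. Enter them one at a time or in small models, because few events are expected.
- **Item missingness at baseline:** relate the missing-data indicator for one scale to the score on another scale, among students for whom that score is observed.
- **Wording:** describe the results in section 2.12 as measured predictors of missingness. No such model can identify dependence on the unobserved values themselves.

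The cost is some analysis code, a sentence or two of text, and a few more exploratory models of limited precision, best reported as estimates with intervals. No new data are needed. Section 2.2 placed the start of data cleaning and analysis after the data had been collected, so the change could be made without affecting the conduct of the study.

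### The stated effect model leaves out the baseline score of the same outcome, so intention-to-treat can mean only analysed by allocated arm among students with a follow-up score

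*Protocol article*

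**What the plan says.** Section 2.12 says the primary outcome will be compared "with an intention-to-treat analysis using a linear mixed model containing a dichotomous intervention group variable". The only other term that the section names for this model is "a random effect for school classes to account for the nested data structure". For the rest, "Secondary outcomes will be compared between the two study arms using analogous linear mixed models". The Abstract describes the effect analyses as "using generalised linear mixed models and intention-to-treat analyses". Neither place names a baseline score, a wave term or a student-level effect, and neither says which survey supplies the response.

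Section 2.10 fixes the measurement times: "Data were collected in both intervention and control classes one week before and one week after the PCS". The baseline outcome is therefore in hand, and Section 2.12 uses it twice: in the comparison of retained and lost students, and in the check of baseline balance between arms.

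Loss is expected. Section 2.10 says "To minimise loss to follow-up, we sent two reminders to encourage participation", and the Limitations describe the pandemic as "potentially affecting response rates due to, inter alia, non-attendance of students". The retention measure in Section 2.9.1 is "Proportion of students in participating classes completing both baseline and follow-up surveys", with no split by arm named. The retention regression in Section 2.12 does not name arm as a predictor.

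Under Section 2.7, teachers with two classes tossed a coin, while teachers with one class chose its arm freely. The Objectives make parameter estimation a secondary aim.

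**The concern.** A model with one follow-up score per student, an arm term and a class effect takes nothing from the baseline survey. A student who answered only the baseline survey is absent from it. A student who answered both is treated as though the first answer were unknown.

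Three things are at stake.

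- **Precision.** With 12 classes the estimate is noisy, and the baseline score normally explains a good part of the follow-up score.
- **Bias from loss.** Participation is voluntary and nobody in the schools is blinded. If students with low climate intentions drop out more in one arm than in the other, the students compared at follow-up already differed at baseline.
- **Bias from allocation.** Where a teacher chose the arm, the arms may differ at baseline, and a model without the baseline score passes much of that difference into the effect estimate.

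The Discussion says the estimates are meant to guide the main study's sample size and may feed into sample-size estimation for similar programmes.

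**Working it through.** **1. The plan's own figure.** Section 2.11 aims for 15 classes of 10–15 students: 15 × 10 = 150 and 15 × 15 = 225, which reproduces the stated 150–225. The 12 classes recruited (7 intervention, 5 control) would give 120–180 at that class size. The article states no SD, intraclass correlation, effect size or loss rate, so every input below is an assumption.

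**2. Possible readings of the response.** Section 2.12 does not name the time point.
- *Follow-up score:* students without one drop out, and the baseline adds nothing. Students who answered only the follow-up do enter, so this is an available-case analysis at follow-up.
- *Change score:* students missing either survey drop out.
- *Both waves stacked, arm and class only:* the arm coefficient averages scores from before and after the programme, and a student's two answers count as independent within class.

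None of these both keeps every student with any data and isolates the post-programme contrast.

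**3. Bias from loss.** Take a standard-normal baseline score, a true effect of 0, and loss that is logistic in the baseline score. Then

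bias = ρ × (mean baseline of retained intervention students − mean baseline of retained control students),

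where ρ is the baseline–follow-up correlation (assumed 0.5–0.7). The log-odds of loss fall by b per SD of baseline intention. Numerical integration gives the mean baseline of the retained:

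| Loss | b = 0 | b = 0.5 | b = 1 |
|---|---|---|---|
| 10% | 0 | 0.049 | 0.091 |
| 20% | 0 | 0.096 | 0.173 |
| 30% | 0 | 0.143 | 0.253 |

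For example, 10% loss in control, 30% in intervention, b = 1 and ρ = 0.6 give 0.6 × (0.253 − 0.091) = 0.097 SD. The full set:

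| Scenario | Bias (SD units) |
|---|---|
| Any loss rates, loss unrelated to baseline | 0 |
| Equal loss, same dependence in both arms | 0 |
| 10% vs 20%, b = 0.5 | 0.024–0.033 |
| 10% vs 20%, b = 1 | 0.041–0.058 |
| 10% vs 30%, b = 0.5 | 0.047–0.066 |
| 10% vs 30%, b = 1 | 0.081–0.113 |
| About 29% loss in each arm, dependence in one arm only (b = 0.8) | about 0.13 |
| Equal loss of 20–30%, opposite dependence (ρ = 0.6) | 0.12–0.30 |

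In these scenarios loss depends only on baseline and arm, so a correctly specified model that conditions on the baseline score, or models both waves jointly, has no bias in theory. Neither helps if loss depends on the unseen follow-up score.

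**4. Precision.** Assume 12 students per class, 29% lost (12 × 0.71 = 8.52 remaining), and variance components of 0.10 for class, 0.54 for student and 0.36 residual. The 7:5 split gives the factor 1/7 + 1/5 = 0.343.
- *Arm plus class, follow-up only:* √[0.343 × (0.10 + 0.90/8.52)] = √(0.343 × 0.2056) = 0.27 SD.
- *Change between waves, class effect constant over waves:* √[0.343 × (2 × 0.36/8.52)] = √(0.343 × 0.0845) = 0.17 SD.
- *The same with variance τ moved from class to class-by-wave:* √[0.343 × (2τ + 0.0845)]. With τ = 0.02 this is √(0.343 × 0.1245) = 0.21 SD; with τ = 0.05 it is √(0.343 × 0.1845) = 0.25 SD.

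Simulation under these components agrees: 0.268 against 0.171 SD with a constant class effect. If class-by-wave variation exists but is left out of the joint model, the model still reports only 0.170–0.177, and false-positive rates reach about 10–16%. The joint model therefore needs that term, and the gain is smaller than a constant class effect would suggest.

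**The case against.** The strongest reply is that the article is condensed. It says the model contains an arm variable and a class effect, not that it contains nothing else, and analysis sets and imputation may be set out in a document not shown. That stands: the absence of a missing-data method is not a fault here. What remains is that the article does specify an effect model, and the baseline score is not in it.

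A reader might infer that the intention-to-treat label is false, or that this is a complete-case analysis. The documents do not support either. The label commonly means analysed as allocated, which matters here because teachers choose which components their class takes up (Section 2.5). The article never claims that every allocated student will have an outcome. And students who answered only the follow-up survey can enter the model.

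A reader might also infer that different loss rates in the two arms would by themselves bias the result. They would not: loss must also relate to the outcome. The pandemic absence mentioned in the Limitations gives no reason to expect that to differ by arm.

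Finally, effect estimation is secondary. Section 2.11 and the Discussion already treat pilot-based sample sizes with caution and plan to combine them with external evidence. The Limitations concede possible imbalance from allocation, though they say nothing about loss. This limits the importance of the point but does not remove it.

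**Conclusion.** The point holds in a limited form. The stated model makes no use of a baseline score that is collected and used elsewhere in the same section. The label can then cover only students with a follow-up score, analysed by allocated arm.

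Bias from loss is 0 if loss is unrelated to intention, or if it is equal and equally related in both arms. It is about 0.02–0.11 SD if loss is unequal and related to baseline. It is larger only if the dependence itself differs between arms: about 0.13 SD if present in one arm only, and 0.12–0.30 SD if the arms run in opposite directions. Even 0.13 SD is about half the estimate's own spread of 0.27 SD. Under the assumed variance components, using the baseline lowers that spread to between 0.17 and 0.25 SD, depending on class-by-wave variation. No size can be given for bias from teacher-chosen allocation, because the article gives no baseline data.

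All these sizes rest on assumed loss, correlation and variance inputs. The consequence is confined to the preliminary parameter estimates; recruitment, retention, data collection and data quality are untouched. The change is worth making because it is cheap: Section 2.2 places cleaning and analysis from May 2022, after both surveys were collected.

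**What to change.** In Section 2.12, or in the analysis plan:

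1. State that the response is the follow-up score, which students are included, and that intention-to-treat means analysed as allocated.
2. Either add the baseline score of the same outcome as a covariate in the primary and secondary models, or model both waves jointly with wave, arm, arm-by-wave and random effects for student, class and class-by-wave.
3. Report loss to follow-up by arm.
4. Keep the arm-plus-class model as a sensitivity analysis, labelled as available-case at follow-up.

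The cost is a few sentences and a little more analysis on data already collected. There are also limits:

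- The covariate version drops students without a baseline score; the joint model keeps them.
- Both assume that loss is explained by observed scores, and do not cover loss that depends on the unseen follow-up score.
- Neither fully removes confounding from teacher-chosen allocation.
- With 12 classes the class-by-wave variance will be poorly estimated, so the resulting standard errors should be read with caution.
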